## Abstract

**Background:**

In Canada, 30%-60% of patients presenting to emergency departments are ambulatory. This category has been labeled as a source of emergency department overuse. Acting on the presumption that primary care practices and walk-in clinics offer equivalent care at a lower cost, governments have invested massively in improving access to these alternative settings in the hope that patients would present there instead when possible, thereby reducing the load on emergency departments. Data in support of this approach remain scarce and equivocal.

**Objective:**

The aim of this study is to compare the value of care received in emergency departments, walk-in clinics, and primary care practices by ambulatory patients with upper respiratory tract infection, sinusitis, otitis media, tonsillitis, pharyngitis, bronchitis, influenza-like illness, pneumonia, acute asthma, or acute exacerbation of chronic obstructive pulmonary disease.

**Methods:**

A multicenter prospective cohort study will be performed in Ontario and Québec. In phase 1, a time-driven activity-based costing method will be applied at each of the 15 study sites. This method uses time as a cost driver to allocate direct costs (eg, medication), consumable expenditures (eg, needles), overhead costs (eg, building maintenance), and physician charges to patient care. Thus, the cost of a care episode will be proportional to the time spent receiving the care. At the end of this phase, a list of care process costs will be generated and used to calculate the cost of each consultation during phase 2, in which a prospective cohort of patients will be monitored to compare the care received in each setting. Patients aged 18 years and older, ambulatory throughout the care episode, and discharged to home with one of the aforementioned targeted diagnoses will be considered. The estimated sample size is 1485 patients. The 3 types of care settings will be compared on the basis of primary outcomes in terms of the proportion of return visits to any site 3 and 7 days after the initial visit and the mean cost of care. The secondary outcomes measured will include scores on patient-reported outcome and experience measures and mean costs borne wholly by patients. We will use multilevel generalized linear models to compare the care settings and an overlap weights approach to adjust for confounding factors related to age, sex, gender, ethnicity, comorbidities, registration with a family physician, socioeconomic status, and severity of illness.

**Results:**

Phase 1 will begin in 2021 and phase 2, in 2023. The results will be available in 2025.

**Conclusions:**

The end point of our program will be for deciders, patients, and care providers to be able to determine the most appropriate care setting for the management of ambulatory emergency respiratory conditions, based on the quality and cost of care associated with each alternative.

**International Registered Report Identifier (IRRID):**

PRR1-10.2196/25619

## Introduction

### The Problem: Emergency Department Overuse and Misuse

Emergency departments (EDs) are specialized and costly resources designed to provide care for patients with urgent or life-threatening conditions [1]. In Canada, low-acuity ambulatory patients, who do not require a gurney or constant observation, represent 30%-60% of all ED visits [2-7]. This situation is increasingly considered as overuse and misuse of ED resources and a threat to the quality of care received by patients whose needs are more urgent [8]. Delays experienced in an overcrowded ED can lead to mortality, morbidity, and reduced quality of life [9-14]. ED overcrowding is widely regarded as a serious but largely avoidable public health risk exacerbated by ambulatory patients [15,16].

### An Important Policy Issue

Many Canadian regional health authorities have developed policies so that low-acuity ambulatory emergency patients preferably present to walk-in clinics or primary care practices [17-19]. Over the past decade, numerous innovations have been implemented to improve timely access to primary care, such as extended walk-in clinic hours [17-19] and the advanced access model (timely access to a care provider) for registered patients [20-26]. In Ontario and Québec, governments have invested massively in new models of primary care to improve access to emergency care and thereby decrease ED visits by patients who are treatable in non-ED settings [18,27]. These health policy priorities rely on the assumption that walk-in clinics and primary care facilities offer less costly, more accessible, and more efficient alternatives to the local population [17,28,29] than overcrowded EDs [3,4,7,8,30-34]. As reasonable as this assumption may appear, data supporting it are scarce and equivocal [35,36].

### Determining the Best Care Setting for Ambulatory Emergency Patients: A Knowledge Gap

Few studies have tested the hypothesis that walk-in or primary care clinics offer better care than EDs to ambulatory patients with acute health concerns.

#### The Costs

A prospective study in Ontario in 2005 [28] concluded that for similar cases, ED costs were 3 to 4 times higher than the costs incurred in a family physician’s office or a walk-in clinic. However, compared costs were not adjusted for comorbidities or severity of disease and did not include out-of-pocket expenses (eg, parking) and indirect costs to patients (eg, loss of income). Other studies, mainly from the United States, have reached similar conclusions [17,37-39] but using charges as proxies of health care costs, which has been shown to be an inaccurate costing method [40,41]. Some reports even suggest that walk-in clinics may in fact increase overall health care costs by duplicating care with frequent return visits after an initial visit [42-45].

#### The Quality of Care

Very few studies have considered quality of care and patient health outcomes in determining the best alternative setting for treating ambulatory emergency patients [8]. A 2017 review (Cochrane) of prospective studies comparing mortality, morbidity, and adherence to practice guidelines in walk-in clinics, primary care practices, and EDs found that none met this criterion [46]. However, three retrospective studies [47-49] and one study evaluating costs and return visits [28] suggested that (1) inappropriate use of antibiotics for self-resolving acute respiratory conditions occurs more frequently following visits to urgent care centers and family medicine offices than to EDs [47-50]; (2) the choice of antibiotics is more concordant with practice guidelines in walk-in clinics than in EDs and family medicine practices [48]; and (3) return visit likelihood within 72 hours is higher after an ED care episode than after any other outpatient clinic visit [28]. However, these fragmented and incomplete data come mostly from the United States. A comprehensive research program comparing acute care received in EDs, walk-in clinics, and primary care practices in Canada is long overdue.

#### The Patient Perspective

Deciders often prioritize certain care settings based on potential cost savings, *auctioning off* care paths to the lowest bidder from the government’s perspective [51]. However, studies have shown that from a patient’s perspective, the choice to seek care in either a primary care practice, a walk-in clinic, or an ED is determined not only by ease of primary care access but also by factors such as convenience and perceived severity of illness and previous health care experiences [35,52-56]. What patients value the most differs considerably from what other stakeholders tend to value [57]. The patient’s perspective must be considered to determine the best ambulatory emergency care option. To our knowledge, no studies have compared these alternative settings from a patient’s perspective.

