#### Selection of Participants

We shall include patients (1) aged 18 years and older; (2) seen in person or via telemedicine in an ED, a walk-in clinic, or the primary care practice where they are registered; (3) ambulatory during the entire visit or consultation; and (4) discharged home with a diagnosis of URTI, sinusitis, otitis media, pharyngitis, tonsillitis, bronchitis, influenza-like illness, pneumonia, acute asthma, or acute exacerbation of COPD. We shall exclude patients (1) transported by ambulance, (2) not covered by the provincial health insurance plan, (3) having consulted for a similar problem in the previous 30 days as patients with refractory diseases representing a population with different care needs, (4) living in a long-term health care facility or incarcerated, or (5) receiving palliative care.

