#### Data Collection and Follow-Up Phone Calls

Research assistants at each site will complete data collection from local medical records. For on-site participants and, where appropriate, for those assessed by telemedicine, they will compile the following information: age, sex, gender, ethnicity, postal code, distance from facility to home, referral by the provincial telephone consultation service (811, Telehealth), enrollment with a family physician, presenting complaints, comorbidities, regular medications, date and time of arrival and discharge, vital signs upon arrival, investigations and interventions during care episode, discharge diagnosis, and prescriptions upon discharge. A follow-up phone call will be made to all participants 10 days after the initial visit to collect data initially unavailable in medical records and to evaluate primary and secondary outcome metrics. Patient-reported outcome and cost measures will be completed by the participants at this moment, either on the phone with the research assistant or independently using a secured online survey link, depending on the participant’s preference. Text messaging and email reminders will be sent to improve participant retention [89]. We shall obtain information on health outcomes (eg, mortality) and physician charges via provincial databases. The charges billed by any physician 7 days after the initial visit will be used to estimate the costs of care for subsequent return visits and hospital admissions.

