#### Statistical Analysis

All main analyses will be conducted primarily on participants assessed in person in any of the care settings. Participants assessed by telemedicine will be analyzed and compared separately between sites where it is implemented. The value delivered at each participating site and on average in each care setting type will be illustrated with an operational effectiveness graphic [114]. Adjusted costs of care for acute ambulatory respiratory conditions will be plotted on the x-axis and adjusted return visits within 72 hours on the y-axis. Points closest to 0 on both axes represent the highest value of care (Multimedia Appendix 6). Indeed, the lower the return visit proportion and cost of care, the higher the value of care. Similar graphics will be used for patient-centered outcome measures. To compare EDs, walk-in clinics, and primary care physician practices, multilevel generalized linear models will be used with probability distributions adapted to the outcome under evaluation. To adjust for confounding (differences in case mix between care settings), an overlap weights approach [115,116] will be used, wherein each individual receives a weight factor that is proportional to the inverse of the probability of choosing a particular setting. Subjects that differ fundamentally between settings are attributed a weight of 0 and are thus excluded. This approach is of the greatest interest when groups are initially very different [116]. Intuitively, overlap weights create a pseudopopulation for which treatment is independent of measured confounders, thus mimicking a randomized trial of those confounders. Overlap weights have been shown to be more robust than conventional inverse probability weighting and matching based on propensity scores [115]. The weights will be estimated using a multinomial logistic regression model in which the dependent variable is the chosen care setting and independent variables are potential confounders or risk factors [117] for the outcomes identified in the literature: age [118,119], sex and gender [118,120], ethnicity [118,121-123], registration with a family physician [20,124], comorbidities (the Charlson index; number of regular medications) [118,125,126], asthma, FEV_1_ among patients with asthma, the Canadian deprivation index [127-129], patient perception of illness severity [130], and vital signs [131-135] as proxies for severity. The same independent variables will be used to adjust for differences in case mix between settings in the telemedicine cohort, excluding vital signs and FEV_1_. Multiple imputation will be considered as a possible means to adjust for these variables in this cohort. Overlap weights will be calculated using the values predicted by this model. We shall verify that the care setting groups are comparable according to the measured confounders after weighting by computing standardized mean differences. Differences below 10% will be considered to indicate good balance [117]. If residual imbalances are present, the weighting model will be revised. Once an appropriate balance is achieved, separate models for each outcome will be fitted to the weighted data, for which the care setting will be the only independent variable. The robustness of results with respect to unmeasured confounding will be assessed using the E-value [136,137]. Clustering by setting (eg, province, practice unit) will be taken into account using multilevel modeling (random intercept on province and practice unit). Reported cost estimates will be calculated with item-specific standardized costs (eg, Québec and Ontario average nurse unit cost). Patients referred to the ED from a participating outpatient facility but discharged home after ED assessment will be analyzed in the care setting group where they first presented, and the ED referral will be considered as a return visit. The costs of any return visits and admissions up to 7 days after the initial visit will be estimated separately and attributed to the care setting where the initial visit took place. Results of the 3 questionnaires from the patient perspective will be reported as proportions (PREM), mean costs (CoPaQ), and median scores (PROM-ED) and adjusted using the overlap weights approach. As patients seek care for symptoms, subanalysis based on presenting complaints instead of discharge diagnosis will be conducted to provide meaningful patient-oriented results. Other subanalyses will evaluate which patient profile (eg, gender [120], motivation for choosing a facility), and institutional characteristics (eg, access to x-ray) predict high quality and low costs, keeping in mind that our value assessment might not yield similar results for all subgroups or even within a group of patients with the same diagnosis. Statistical differences will be assessed with a significance threshold set at .05.

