### Challenges and Mitigation Strategies

First, as patients choose their facility, those presenting at the 3 types of setting will likely represent different populations. However, we believe that the potential confounding bias due to self-selection of the care setting can be overcome using the overlap weights approach. Extensive testing of the robustness of our findings by sensitivity analyses should allow us to avoid reaching false conclusions under the influence of uncontrolled confounding. Second, the Québec and Ontario health systems might differ enough to yield results that will not be easy to generalize. When applicable, the sources of heterogeneity will be investigated. However, Canadian provincial health care systems have fundamental similarities that reduce the risk of poor generalizability. All are based on universal coverage; all suffer from a lack of integration between primary and urgent care resources [138,139]; institutions follow the recommendations of the same accreditation organizations; and care providers are trained according to the same standards and guidelines. Third, because of the pandemic, many outpatient clinics have ceased their activities or shifted to telemedicine. Our research plan already includes participants evaluated by telemedicine and will adapt easily to any increase in this practice. If the pandemic is still ongoing in November 2021 when phase 1 is launched, we will be able to collect financial data from participating institutions, which can be done remotely. Time measurement of care processes can be postponed until phase 2 in 2023, during which the recruitment of participants is planned. Finally, if the pandemic is still a factor in 2023, we will select clinics that continue to assess patients with acute respiratory disorders.

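### The weighting model, which carries all the confounding control, omits prior health care use and so may bias the return-visit and 7-day cost comparisons

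*Protocol article*

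**What the plan says.** The Patient Perspective section of the Introduction says that choice of setting depends on ease of access to primary care and also on "factors such as convenience and perceived severity of illness and previous health care experiences".

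Statistical Analysis gives a rule for the weighting model: its "independent variables are potential confounders or risk factors [117] for the outcomes identified in the literature". It then lists age, sex and gender, ethnicity, "registration with a family physician [20,124], comorbidities (the Charlson index; number of regular medications"), asthma, FEV1 in patients with asthma, the deprivation index, "patient perception of illness severity [130], and vital signs [131-135] as proxies for severity". The outcome models that follow are ones "for which the care setting will be the only independent variable".

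Data Collection and Follow-Up Phone Calls lists what is taken from the records, and no visit history is on that list. On external sources it says "We shall obtain information on health outcomes (eg, mortality) and physician charges via provincial databases". The physician charges it describes are those of the 7 days after the index visit. Prior use enters only once at recruitment, through the exclusion of patients "having consulted for a similar problem in the previous 30 days".

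Challenges and Mitigation Strategies concludes that "the potential confounding bias due to self-selection of the care setting can be overcome using the overlap weights approach".

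**The concern.** Overlap weights balance the variables in the weighting model and nothing else, except so far as other variables are correlated with those. With no covariates in the outcome models, a confounder missing from the list is not adjusted for anywhere else.

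Prior use is a strong candidate for such a confounder. Table 2 defines the primary health outcome as a return to any ED or outpatient clinic. The adjudication committee classifies returns, but the proportion as defined counts all of them. A person who attends often has a higher chance of a visit in any given week, whatever care was given at the index visit. The same person may also be more likely to present at the setting they habitually use. The 7-day cost outcome adds the cost of return visits and so inherits the problem.

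The balance check would give no warning, because standardized mean differences are computed only on measured confounders. At stake is whether a difference between settings reflects the care given or the attendance habits of those who go there.

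**Working it through.** The plan gives no figure for residual confounding, so there is none to reproduce. The benchmark is the target in Sample Size: a 5-point difference in 72-hour return visits, for example 5% against 10%.

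**1. Is prior use covered anywhere?**
- Weighting list: no visit count. The nearest items are registration, the Charlson index and number of medications.
- Registration: primary care patients must be seen at the practice where they are registered. An unregistered patient therefore has almost no chance of being in that group and gets a three-way overlap weight near 0. Registration is then nearly constant in the weighted population and cannot stand in for prior use there.
- 30-day exclusion: covers a similar problem only, not overall attendance.
- Sensitivity analyses: they restrict on age, comorbidity, asthma or COPD, medications, vital signs, deprivation and smoking. None restricts on prior use.
- E-value: states how strong a confounder would have to be, and adjusts for nothing.

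**2. How large could the bias be?** Assume no true setting effect. Let q be the share of habitual attenders in a setting after weighting, and RR their risk ratio for return. With b the risk in other patients, the observed risk is b × (1 + q × (RR − 1)). Set b so that the reference setting as a whole has a 5% risk. The values of q and RR are assumptions; the documents give neither.

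| RR | q reference | q other | Observed risk, other setting | Spurious difference |
|---|---|---|---|---|
| any | 20% | 20% | 5.0% | 0 |
| 2 | 10% | 20% | 5% × 1.2/1.1 = 5.45% | 0.5 points |
| 2 | 10% | 30% | 5% × 1.3/1.1 = 5.91% | 0.9 points |
| 3 | 10% | 30% | 5% × 1.6/1.2 = 6.67% | 1.7 points |
| 4 | 10% | 30% | 5% × 1.9/1.3 = 7.31% | 2.3 points |
| 4 | 10% | 50% | 5% × 2.5/1.3 = 9.62% | 4.6 points |

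The moderate rows (RR 2 to 3, gap 10 to 20 points) give 0.5 to 1.7 points, which is 9% to 33% of the target. The last row is extreme.

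**3. Is an effect of background attendance plausible?** Assume visits follow a Poisson process.
- 12 visits a year: 1 − exp(−12 × 3/365) = 9.4% within 72 hours, and 1 − exp(−12 × 7/365) = 20.6% within 7 days.
- 2 visits a year: 1.6% and 3.8%.
- A 10- to 20-point gap in the share of the heavier users gives (9.4 − 1.6) × 0.10 to 0.20 = 0.8 to 1.6 points at 72 hours, in line with the moderate rows.

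**4. What would the E-value show?** For the target ratio of 2 it is 2 + √(2 × 1) = 3.4, so a confounder would have to be strong to explain all of a 5% against 10% result. For 6.67% against 5%, a ratio of 1.33, it is 1.33 + √(1.33 × 0.33) = 2.0. Smaller differences are easier to explain away.

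**The case against.** The strongest reply is that the document does not name prior use at all. It names experiences, in a passage about patients' views, and experience is not visit volume. A reader might infer that the protocol contradicts itself by naming a confounder and then leaving it out. The text does not support that: the step from experiences to visit counts is an inference, though a reasonable one.

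Nor do the documents show that prior use predicts return after an acute respiratory visit, or that it differs between settings after the listed adjustment. The covariates were taken from cited literature not available here. This stands, and it limits the claim to possible bias.

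There is also real mitigation. The 30-day exclusion removes the prior visits closest to the outcome. Adjudication separates planned from unplanned and avoidable from unavoidable returns. The exclusions on comorbidity, medication and deprivation act on correlates of frequent use. Motivation for choosing the setting is recorded and used in subanalyses. These soften the gap without closing it, since none measures or balances overall prior attendance.

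Finally, this is a condensed article, and a fuller plan may add covariates. But the article does not leave the list open. It states the rule, the covariates and the form of the outcome models, and then claims that self-selection bias can be overcome.

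**Conclusion.** The point holds as a possible bias that is worth removing. Prior health care use is absent from the weighting list, the listed baseline data and the sensitivity analyses, while the weights carry all the adjustment and the outcome can pick up background attendance.

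The moderate estimate of 0.5 to 1.7 points rests on assumed shares and risk ratios. Over the wider assumed range it runs from 0 to 4.6 points. The direction is unknown, because habitual ED users could inflate returns after ED visits while habitual clinic users could do the same for the clinics.

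Two stronger readings should be resisted. One is that habitual attenders do bias the primary contrast; nothing in the documents establishes that. The other is a larger headline figure. Taking 5% as the risk in patients who are not habitual attenders, with RR 4 and a 20-point gap, gives 5% × 3 × 0.20 = 3.0 points. If 5% is the risk of the whole reference setting, as the sample size example suggests, the same risk ratio and gap (30% against 10%) give 2.3 points.

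**What to change.** 1. Extend the planned provincial billing extraction back 12 months before the index visit, and make sure that the consent wording covers it before recruitment starts.
2. Add the number of prior ED visits to the multinomial weighting model and to the standardized-mean-difference check, leaving out visits on the index day.
3. Add the number of prior outpatient visits where overlap allows. Since primary care patients must be registered at that practice, this count may strongly predict that group. Check overlap, report the effective sample size, and show results with and without it.
4. Consider adding referral by the provincial telephone service (811/Telehealth), which is already recorded.
5. Reword Challenges and Mitigation Strategies to say that weighting addresses measured confounding only, with the E-value describing robustness to the rest.

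The cost is a longer date range in a data request already planned, the consent wording, and some loss of effective sample size or overlap. A richer model may also narrow the population to which the weighted results apply. No extra patients are needed. The same look-back would let the 30-day exclusion be checked from one type of source in all three settings.
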